##### Research question 3: cost-effectiveness of telemedicine in patient subgroups

For research question 3, costs, utility, QALYs, ICER and willingness-to-pay curves will be computed to estimate the difference in cost-effectiveness between users and non-users of telemedicine in general. Subsequently, the analyses will be repeated to estimate cost-effectiveness in subgroups, similar to the groups defined for research question 2 in the clinical effectiveness analysis.

##### Research question 4: cost-effectiveness of different telemedicine components

For research question 4, costs, utility, QALYs, ICER and willingness-to-pay curves will be computed to estimate the difference in cost-effectiveness between components of telemedicine, similar to the comparisons defined for research question 3 in the clinical effectiveness analysis.

### Sample size calculation

The primary focus in RELEASE-HF is on the clinical effectiveness of telemedicine in HF management. Hence, the sample size calculation is based on parameters relevant to this analysis. The sample size calculation was conducted in three steps: (1) computing the required sample size for the main effect of telemedicine on the primary outcome, (2) taking into account that subgroup effects are of primary interest and (3) anticipating the accrual rate.

For the first part, we assumed a mean increase in the number of days spent alive without unplanned hospitalisation of 6.4 (SD 21.1) days based on the findings of the TIM-HF2 study.^44^ This corresponds to a required sample size of 432 patients in total, based on a type I error probability of 5%, a type II error probability of 20% and accounting for 20% dropout.

Such a sample size would allow for an overall estimate of the difference between telemedicine and no telemedicine in days spent alive without unplanned hospitalisation in the overall patient population; however, our interest is in heterogeneous intervention effects. Hence, for the second part, the sample size was inflated to estimate subgroup effects.^50 51^ To detect interaction effects that are 50%–60% of the size of the overall effect (ie, increase of more than 3.2–3.8 days spent outside the hospital due to the interaction given the main effect) with a power of 80%, the required sample size is inflated by a factor of 12.^50^ This results in a required sample size of 5184 individuals.

Finally, from the HF registry pilot study (CHECK-HF), we know that, in view of the estimated average number of patients per hospital, the average proportion of included outpatient clinic patients with HF was above 80%.^52^ Taking this accrual rate into account, we would require the inclusion of 6480 patients with HF.

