##### Preparation of the statistical model

As a first step, we describe how the overall effect of offering any type of telemedicine versus not offering telemedicine will be estimated. This analysis will subsequently be used for a comparison of telemedicine effects on days alive without unplanned HF-related hospitalisation during 1 year across subgroups.

The cohort is restricted to individuals with newly diagnosed HF, that is, at most 3 months prior to baseline. The exposure contrast is defined as offering any type of telemedicine after first presentation with HF at the hospital outpatient clinic versus patients not offered telemedicine. The telemedicine status for the entire follow-up is defined by 6 months after baseline measurement of telemedicine, used as an observational analogue of an ‘intention to treat’ analysis in which the stopping of telemedicine is disregarded.

Because telemedicine administration is dependent on patient characteristics, confounding by indication will be accounted for. Based on clinical consensus, the following patient-level confounding variables measured at baseline will be adjusted for: age, sex, SES, BMI, NYHA, LVEF, aetiology of HF, systolic blood pressure, diastolic blood pressure, heart rhythm, heart rate, chronic respiratory disorders, OSAS, stroke, extra cardiac arterial vascular pathology, DM, hypertension, anaemia, CKD, malignancy, heart rhythm disorders, depression and thyroid disease (see table 3 and online supplemental material 1).

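### The stated 80% power for interactions of 50–60% of the main effect is not reached across that range, and the count makes no allowance for restricting the main analysis to newly diagnosed patients

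*Protocol article*

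**What the plan says.** The Sample size calculation has three steps.

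- **Main effect.** It assumes a "mean increase in the number of days spent alive without unplanned hospitalisation of 6.4 (SD 21.1) days", taken from a cited trial. With 5% type I error, 80% power and a 20% allowance for dropout, the plan then concludes: "This corresponds to a required sample size of 432 patients in total".
- **Subgroup effects**, described as the primary interest. "To detect interaction effects that are 50%–60% of the size of the overall effect" (given as 3.2–3.8 days) "with a power of 80%, the required sample size is inflated by a factor of 12". The result is 432 × 12 = 5184.
- **Accrual.** An 80% inclusion proportion from the registry pilot is applied: 5184 / 0.8 = 6480. "Taking this accrual rate into account, we would require the inclusion of 6480 patients with HF". The Abstract also gives 6480 as the planned enrolment.

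For the analysis, Preparation of the statistical model says: "The cohort is restricted to individuals with newly diagnosed HF, that is, at most 3 months prior to baseline". The section on research question 2 applies the same limit. The entire cohort is analysed only as an additional analysis. The Study population section admits anyone meeting the HF criteria, including patients diagnosed elsewhere.

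The same model section subtracts days in hospital or dead from 365. Table 1 subtracts only HF admission days.

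**The concern.** The study is sized on subgroup interactions, so the power figure attached to them is the one readers will rely on. Three things about it do not fit.

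- A single factor of 12 cannot give 80% power at both ends of a 50–60% range, because the sample needed changes with the square of the interaction size.
- The 5184 and 6480 count a wider population than the one entering the main analysis.
- An SD of 21.1 days is small for an outcome in which one early death can remove most of a year.

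The stake is how subgroup results are interpreted: a contrast that shows nothing carries less information than 80% power suggests.

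**Working it through.** **Inputs.** Effect 6.4 days, SD 21.1, type I error 5% (taken as two-sided, which reproduces the plan), power 80%, dropout 20%, factor 12, accrual 80%: all from the Sample size calculation. Assumed because not stated: 1:1 exposure, 50:50 subgroups, and an interaction read as the difference between two subgroup effects.

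**1. The plan's own chain.** n per arm = 2 × (1.960 + 0.842)² × (21.1/6.4)² = 170.7, so 171 per arm and 342 in total; 342 / 0.8 gives 428 (430 with the t distribution). The stated 432 is close enough. 432 × 12 = 5184 and 5184 / 0.8 = 6480 are exact.

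**2. Factor needed.** In the balanced layout the interaction contrast has 4 times the variance of the main effect. For an interaction of r times the main effect, the factor for 80% power is 4/r².

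- r = 0.50: 4/0.25 = 16, so 432 × 16 = 6912 (8640 after dividing by 0.8)
- r = 0.60: 4/0.36 = 11.1, so 4800 (6000 after dividing by 0.8)
- Factor 12 corresponds to r = √(4/12) = 0.577

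**3. Power delivered.** Power = Φ(δ / (4 × 21.1/√n) − 1.960), with n analysed. The difference detectable with 80% power is 2.802 × 4 × 21.1/√n.

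| Enrolled | Analysed (× 0.8) | Power at 3.2 days (50%) | Power at 3.84 days (60%) | 80% reached from |
|---|---|---|---|---|
| 5184 | 4147 | 68.5% | 83.4% | 3.67 days (57%) |
| 6480 | 5184 | 77.9% | 90.6% | 3.28 days (51%) |

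Scaling from the plan's 432 instead gives 67.9% and 82.9% at factor 12. Imbalance lowers these figures: with 4147 analysed, 30% on telemedicine and a 30% subgroup, power is 54% at 50% and 69% at 60%.

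**4. Newly diagnosed restriction.** The document gives no share, so these are assumed values, with n multiplied by the share:

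| Share newly diagnosed | Base analysed | Power at 50% | Power at 60% |
|---|---|---|---|
| 80% | 4147 | 59% | 75% |
| 50% | 4147 | 41% | 55% |
| 30% | 4147 | 27% | 36% |
| 50% | 5184 | 49% | 64% |

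Even at the 60% end, 80% power needs about (2.802 × 4 × 21.1/3.84)² ≈ 3790 newly diagnosed patients analysed. That is 91% of 4147 or 73% of 5184.

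**5. SD once death counts.** If a share m dies, evenly over the year, the variance from death alone is m × 365²/3 − (182.5 × m)².

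- m = 1%: 444.1 − 3.3 = 440.8, SD 21.0
- m = 2%: SD 29.6
- m = 5%: SD 46.2

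So 21.1 is used up at about 1% mortality, before any hospital day is added. With the 6.4-day effect held fixed and 4147 analysed, power at 50%/60% would be 41/55% at 2% mortality and 20/27% at 5%.

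**The case against.** Several points on the other side are fair.

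- **The range is partly covered.** A reader might infer that the power claim fails throughout 50–60%. It does not: the upper end is met under either enrolment figure. With 6480 enrolled, as the Abstract and the sample size section both say, the shortfall at 50% is about 2 percentage points. This stands and limits the arithmetic point.
- **6480 as a screening number.** Because the 80% is a proportion of clinic patients included, a reader might take 6480 as the number to approach. The document twice gives it as the number enrolled or included and describes no screening stage, so this reading is not supported. It does matter whether 5184 or 6480 will be enrolled.
- **The SD.** A reader might conclude that 21.1 is impossible. That needs a mortality rate, which the document does not give. Table 1 does not subtract death, and the effect and SD come from a cited trial that is not at hand. Only the conditional statement holds.
- **The newly diagnosed share may be high.** The Abstract places the baseline measurement at HF diagnosis, which allows for this. But the plan also admits patients diagnosed elsewhere and compares diagnosis up to 3 months with longer, so it expects some of the latter.
- **No decision rule depends on the power.** The Abstract calls the stratified analyses exploratory, and nothing says that null contrasts will be read as uniform benefit. This lowers the stakes, but the power sentence still needs to be right because the study is sized on it.

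**Conclusion.** The power statement is wrong as written, to a limited and calculable extent. In the most favourable layout, power at the 50% end is 68% if 5184 are enrolled and 78% if 6480 are. The claim holds only from about 3.7 or 3.3 days respectively, not from 3.2.

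The missing allowance for the newly diagnosed restriction holds under either enrolment figure and could matter more, but its size cannot be computed from the document. The percentages given for it rest on assumed shares.

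The SD point is conditional: 21.1 is compatible with the outcome as modelled only if one-year mortality is about 1% or less, with deaths spread evenly over the year.

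The multiplication from 432 to 5184 to 6480 is not in dispute.

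**What to change.** No extra enrolment is needed.

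- State clearly whether 6480 is the number enrolled. Give the interaction detectable with 80% power for that number (about 3.3 days if 6480, about 3.7 days if 5184), and say that it assumes balanced exposure and subgroups.
- Express the target as newly diagnosed, analysable patients, and give the detectable interaction for the newly diagnosed share seen in the registry.
- Estimate the SD of the outcome as modelled, deaths included, from pooled registry data without looking at exposure, and restate the detectable effect. Align Table 1 with the model section on whether days after death are subtracted.

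The cost is some rewording of the sample size section, one blinded data summary, and a less favourable power statement.

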**Methods and analysis:**

The RELEASE-HF (‘REsponsible roLl-out of E-heAlth through Systematic Evaluation – Heart Failure’) study is a multicentre, observational, registry-based cohort study that plans to enrol 6480 patients with HF using data from the HF registry facilitated by the Netherlands Heart Registration. Collected data include patient characteristics, treatment information and clinical outcomes, and are measured at HF diagnosis and at 6 and 12 months afterwards. The components of telemedicine are described at the hospital level based on closed-ended interviews with clinicians and at the patient level based on additional data extracted from electronic health records and telemedicine-generated data. The costs of telemedicine are calculated using registration data and interviews with clinicians and finance department staff. To overcome missing data, additional national databases will be linked to the HF registry if feasible. Heterogeneity of the effects of offering telemedicine compared with not offering on days alive without unplanned hospitalisations in 1 year is assessed across predefined patient characteristics using exploratory stratified analyses. The effects of telemedicine components are assessed by fitting separate models for component contrasts.

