### Study population

The HF registry comprises patients admitted to a Dutch hospital or to an outpatient clinic for HF irrespective of telemedicine use (figure 1). All patients who meet the diagnostic criteria for HF and its phenotype, according to the European Society of Cardiology (ESC) 2021 guidelines on HF, are included.^1^ If a patient has been diagnosed with HF in a setting other than the one where the patient currently presents (primary, secondary or tertiary care), the patient will also be included.^31^ Current HF registry is not yet incorporated and implemented in care pathways in EHR systems; therefore, selected patients fulfilling the NHR criteria are included in the HF registry and not on a consecutive basis or full coverage of all patients at the outpatient HF clinic. This may lead to selection bias. To prevent this selection bias, a researcher of RELEASE-HF is alerting healthcare professionals regularly to include all patients with HF in the HF registry, regardless of their telemedicine use, treatment and disease severity. Additionally, national working groups are progressing to fully incorporate the HF registry into the EHR.

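### The last sizing step divides by the registry's coverage of clinic patients, so 6480 is an eligible pool and the derived number of inclusions is 5184

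*Protocol article*

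**What the plan says.** The section Sample size calculation proceeds in three steps.

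1. For the main effect it assumes a "mean increase in the number of days spent alive without unplanned hospitalisation of 6.4 (SD 21.1) days", "based on a type I error probability of 5"% and "a type II error probability of 20"%. With an allowance for 20% dropout it arrives at 432 patients in total.
2. To detect interactions of 50% to 60% of the main effect with 80% power, it multiplies by 12: "This results in a required sample size of 5184 individuals".
3. It then cites the registry's pilot study, where "the average proportion of included outpatient clinic patients with HF was above 80"%. It calls this an accrual rate and concludes: "Taking this accrual rate into account, we would require the inclusion of 6480 patients with HF".

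The abstract, under Methods and analysis, says the study "plans to enrol 6480 patients with HF using data from the HF registry". On the current registry, the section Study population says that selected patients are "included in the HF registry and not on a consecutive basis or full coverage of all patients at the outpatient HF clinic". The section HF registry likewise describes data collection as non-consecutive.

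**The concern.** Two kinds of loss matter when a cohort is sized. Loss after inclusion (dropout, missing outcome) raises the number that must be included. Loss before inclusion (eligible patients who are never registered) raises the number of eligible patients who must be available, and leaves the required number of inclusions unchanged.

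The proportion in step 3 is of the second kind, since a clinic patient who is not entered in the registry never becomes an inclusion. The plan treats it as if it were of the first kind and labels the result as inclusions. The first kind of loss has already been counted in step 1.

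What is at stake is the meaning of the study's headline number. 6480 is the figure against which readers, funders and hospitals will judge recruitment, and the derivation given for it supports a different quantity.

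**Working it through.** **Inputs** (all from Sample size calculation): difference 6.4 days, SD 21.1, type I error 5%, power 80%, dropout 20%, inflation factor 12, coverage 0.80. The article does not state sidedness or the ratio of exposed to unexposed patients. Two-sided testing and 1:1 groups are assumed here.

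**Step 1, is dropout already inside the 432?**
- n per group = 2 × 21.1² × (1.960 + 0.842)² / 6.4² = 170.6, so 171 per group and 342 in total.
- Dividing by (1 − 0.20): 342 / 0.80 = 427.5, so 428. A t-based calculation gives 172 per group, and 344 / 0.80 = 430.
- The stated 432 is within about 1% of both. The 20% dropout is therefore inside the 432 and carries into every later figure.

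**Step 2.** 432 × 12 = 5184, exactly as stated. After 20% dropout, 5184 × 0.80 ≈ 4147 remain for analysis.

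**Step 3.** 5184 / 0.80 = 6480, exactly as stated. Multiplying by 1.20 instead would give 6221, so the step is a division by 0.80.

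**What the quotient means.** If coverage c is the proportion of clinic patients who are included, then

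inclusions = c × eligible clinic patients, so eligible clinic patients = inclusions / c.

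With inclusions = 5184 and c = 0.80, the eligible clinic patients number 6480. The required inclusions are the input to this calculation and stay at 5184. As the plan says coverage was above 80%, the pool could be smaller: 5184 / 0.85 = 6099, or 5184 / 0.90 = 5760.

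**The two readings of 6480**

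| 6480 taken as | Included | Left after 20% dropout | Against the derived 5184 inclusions |
|---|---|---|---|
| Eligible pool at 80% coverage | 5184 | about 4147 | met exactly |
| Patients enrolled | 6480 | 5184 | exceeded by 1296 (1296 / 5184 = 25%) |

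6480 would be the right number of inclusions only if a second 20% were lost after inclusion, on top of the dropout in step 1. The article names no such loss.

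**The case against.** **The arithmetic is correct and the error is in the safe direction.** Both points stand. Every figure reproduces, and under either reading in the table the plan's own requirement is met or exceeded.

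**A reader might infer that the N behind the 80% power claim is ambiguous by 25%.** The document does not support that. The power statement belongs to step 2 and to 5184; the 6480 comes afterwards and carries no power claim. Nor does the article itself ever call 6480 a patient pool: it speaks of inclusion in one place and enrolment in the other.

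**A reader might also infer that this step costs power.** With equal exposure groups and two equal subgroups, the interaction has standard error 4 × 21.1 / √N. At N = 4147 analysed, power is then about 68% for an interaction of 50% of the main effect and 83% for one of 60%. Those values describe the plan's own step 2 result. Under the same assumptions the inflation factor is 4 / r², which is 16 at r = 0.5 and 11.1 at r = 0.6, so the shortfall at 50% reflects the choice of 12 and not the division by coverage. Nor can a loss be worked out for some lower coverage, because the documents give no coverage figure for the current registry.

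**The 80% might be the share of included patients who are outpatients.** Dividing inclusions by 0.80 would then be right. Study population admits both hospitalised and outpatient patients, so the reading is not absurd. But the article calls the figure an accrual rate and relates it to the estimated number of patients per hospital, which describes uptake from a clinic population. The coverage reading fits the text better.

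**The surplus might cover other losses after inclusion**, such as the restriction of the main analysis to patients diagnosed within 3 months before baseline. The article does not say so, and clinic coverage does not measure that restriction.

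**Conclusion.** The point holds as an error of derivation and labelling in the headline sample size. By the plan's own steps the required inclusions are 5184, and 6480 is the eligible clinic population needed at 80% coverage. The difference is 1296 patients, or 25% of the derived requirement.

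The error is conservative and does not by itself undermine the stated 80% power. It is worth correcting because 6480 is the published target and does not follow as a number of inclusions.

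The conclusion rests on reading the pilot proportion as coverage of clinic patients, which the wording favours. The check that dropout sits inside the 432 also assumes two-sided testing and equal exposure groups.

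As a pool figure, 6480 carries one further assumption: that the current registry reaches the pilot's 80%. The article's own account of non-consecutive, incomplete registration means this should be checked. It does not show what the coverage is.

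**What to change.** Choose one of two statements in Sample size calculation:

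- **5184 as required inclusions.** Describe 6480 as the eligible clinic population expected to yield them at an assumed 80% coverage, and check that assumption against the coverage seen in the current registry.
- **6480 as a deliberate enrolment target.** Drop the coverage rationale, and state that the target exceeds the derived requirement by 1296 and leaves about 5184 for analysis after 20% dropout.

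In either case, align the abstract and count recruitment in registered inclusions.

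The cost is one paragraph and one sentence of the abstract; no extra patients or data are needed. The first option lowers the headline target and gives up a margin that may be useful, since the main analysis is restricted to newly diagnosed patients. The second keeps that margin and changes only its justification.

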### Patient and public involvement

Patient and public organisations were involved during grant application. Public organisations were involved in recruiting hospitals, and in legal support and advice. Healthcare professionals’ involvement in the study includes participating in an interview about telemedicine and motives about telemedicine choice and use. Patients with HF and patient organisations will be involved in formulating and prioritising relevant research questions which are in line with the need of the patient and the aim of the RELEASE-HF study. The results will be disseminated with involvement of patient and public organisations.

## Ethics and dissemination

### Management and storage of data

RELEASE-HF is an observational, retrospective multicentre cohort study of prospectively collected data registered within the NHR. A waiver for informed consent for analysis of data from the NHR data registry was obtained. Data collection and registration is performed by the participating centres in a secured online environment. Detailed information on the process of data acquisition, completeness, data quality and analysis of the NHR has been published previously.^30^ To obtain reliable data, the NHR has an advanced, certified data quality control system in place to ensure completeness and quality of data.^35^

Participants of the interview study will sign informed consent. Data will be stored in the secured environment at the University Medical Center (UMC) Utrecht, the Netherlands. Data will be pseudonymised at the participant and setting level. A secured identification log will be used, only accessible to the main RELEASE-HF researcher. Because the interview data will be linked to the HF registry, pseudonymised data will also be stored at the Medical Informatics Department of University Medical Centers Amsterdam (the Netherlands).

Storage of linked data sets (HF registry with other national databases) will be part of the infrastructure established by the Heart4Data consortium.^28^ The RELEASE-HF study will follow these principles.

The Medical Ethics Committee of UMC Utrecht (the Netherlands) reviewed the study protocol and confirmed that the study does not fall under the scope of the Medical Research Involving Human Subjects Act. RELEASE-HF complies with the rules of the General Data Protection Regulation.

